##### Subgroup-specific secondary outcomes

Our remaining secondary outcomes are only valid for subgroups of the sample, such as those individuals who report being aware of what an antibiotic is. For all these outcomes the sample can be divided into individuals within the subgroup where the outcome is valid and individuals not in that subgroup. As these subgroups may be at least partly determined post-randomization by the intervention (e.g., the intervention may well affect whether an individual in the intervention group is aware of what an antibiotic is) a standard analysis of the treatment effect, by simply subsetting the data, would be prone to post-randomization selection bias (55). For these secondary outcomes we will therefore use a slightly-modified, regression-based approach that aims to adjust for this potential selection bias when estimating cluster-level treatment effects. In the literature these are known as survivor average causal effects, as these types of methods were originally developed to address selection bias in the context of survival/death creating subgroups of individuals where the outcome is valid or not (e.g., you cannot measure health outcomes if the patient has died) (56).

Our approach aims to estimate the cluster-average causal effect of treatment among the subgroup of individuals who would be part of that subgroup irrespective of any effect of the intervention (e.g., among individuals who would be aware of what antibiotics are irrespective of any effect of the intervention on their awareness of what antibiotics are). As with our whole-sample secondary outcomes, we will compute these treatment effects on both the absolute difference and ratio scales as the difference/ratio in the cluster-level percentage occurrence of the relevant outcome event between treatment groups, among the subgroup of individuals for whom the outcome is valid.

See (56) for full details of the original method. In summary though, we will first fit a generalized linear model with Bernoulli errors and a logit link to the binary indicator of whether an individual is in the subgroup where the ultimate outcome of interest is valid not (e.g., whether they report being aware of what an antibiotic is or not, with the ultimate outcome of interest being whether they report being aware of what ABR is). The model will contain covariates for cluster treatment allocation, subdistrict, sex (female/male), age (years) and age^2^, education level (none, less than primary, primary, less than secondary, secondary or less than higher secondary, higher secondary, graduate/post-graduate), employment status and main role in the last 30 days (no paid/in-kind work, nonprofessional/manual, personal business, professional), ownership of any animals by the household for food/economic purposes (yes/no), number of individuals living in the household, and the cluster-level baseline mean of the relevant secondary outcome. We will then use the model to compute outcome probabilities for every participant and subtract these from 1 to create an adjustment factor that will be used in the next stage to adjust for any selection bias due to the subgroup being determined post-randomization.

We will then subset the data to only include those participants who are in the subgroup for which the ultimate outcome is valid, and then fit a generalized linear model with Bernoulli errors and a logit link to the relevant ultimate secondary outcome of interest (e.g., reported awareness of what ABR is). This model will include covariates for the selection bias adjustment factor and all the covariates included in the first stage model. Unlike in (56) this model will also be weighted by the inverse of the cluster sample sizes to produce cluster-average causal effect estimates (40). Then, as described above (*Effect of engagement with the community dialogue approach intervention*), we will use marginal effects methods to compute survivor average causal effect estimates on the difference and ratio scales. Lastly, we will compute 95% confidence intervals for all these treatment effect estimates based on the same clustered bootstrap approach described above (*Effect of engagement with the community dialogue approach intervention*).

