#### Personal use of antibiotics in the past 3 months for typically viral and self-limiting upper respiratory tract infections

This outcome only applies to the subgroup of individuals in the target population/sample who report being aware of what an antibiotic is, having suffered from either a “sore throat,” “chest cold” or a “common cold” in the past 3 months, and sought treatment for that illness. It is a binary indicator of whether that treatment included any antibiotics or not. These conditions should typically be viral and self-limiting, but it is known that antibiotics are frequently used to treat such conditions in this context, often due to individuals seeking care from informal drug sellers with poor/no training and a strong incentive to sell antibiotics. The CDs therefore emphasize seeking treatment from a qualified provider and only obtaining antibiotics using a prescription. Therefore, this outcome is to allow us to explore whether the CDs may decrease the relative frequency of inappropriate antibiotic use for these conditions among adults in this subpopulation.

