#### Use of antibiotics in the past 3 months by any children (<15) of female community members for typically viral and self-limiting upper respiratory tract infections

This outcome only applies to the subgroup of female individuals, who report being aware of what an antibiotic is, who have one or more children <15 who have suffered from either a “sore throat,” “chest cold” or a “common cold” in the past 3 months, and the child was treated for that illness. The outcome is a binary indicator for each child (who has these characteristics) of whether the treatment included any antibiotics or not. These conditions should typically be viral and self-limiting, but it is known that antibiotics are frequently used to treat such conditions in this context, often due to individuals seeking care from informal drug sellers with poor/no training and a strong incentive to sell antibiotics. The CDs therefore emphasize seeking treatment from a qualified provider and only obtaining antibiotics using a prescription. Therefore, this outcome is to allow us to explore whether the CDs may decrease the relative frequency of inappropriate antibiotic use for these conditions among children in this subpopulation.

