### Sample size

Due to logistical constraints around how many intervention clusters we believed we can implement in, we decided that we could have a maximum of 25 clusters per treatment group. As we plan to sample participants from two villages per cluster, and as we plan to sample an equal number of female and male participants per village, we also decided to sample an even number of participants per cluster. Following discussion among the trial team we decided that for both primary outcomes we would look at cluster-level treatment effects (40), which will mean aggregating the outcome to the cluster level by computing the mean of all survey participants’ percentage knowledge scores for each cluster (which we refer to as the cluster-level mean percentage knowledge score below). Based on discussion among the trial team we targeted being able to detect if the cluster-level mean percentage knowledge score for both outcomes was 15 percentage points or greater in the intervention group compared to the control group. We conservatively assumed an intracluster correlation coefficient of 0.3 for both primary outcomes, based on some related data from this setting in our previous survey study (14). We used the approach of Horzo to estimate plausible values for the overall variance for each primary outcome (41): 40 for the knowledge score measuring the level of correct and appropriate knowledge about antibiotics, ABR, and usage of antibiotics for human illness, and 25 for the knowledge score measuring the level of correct and appropriate knowledge about usage of antibiotics for animal health and antibiotic-related environmental considerations.

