Based on these inputs and using the approach of (42) (based on formula 2 and assuming a cluster-level analysis), we then looked at a range of sample size scenarios. We adjusted the standard alpha level of 0.05 to 0.025, following a Bonferroni approach to account for the multiple testing of two primary outcomes. From these results we will aim to sample 44 participants per cluster (22 per village), so 1,100 participants across 25 clusters per treatment group and 2,200 participants across all 50 trial clusters, for the baseline and endline surveys. Conditional on these assumptions, when comparing between the treatment groups at endline we will have 90% power to detect a 14-percentage-point or greater difference between each group’s mean cluster-level percentage knowledge score regarding correct and appropriate knowledge about antibiotics, ABR, and usage of antibiotics for human illness, and 90% power to detect a 11-percentage-point or greater difference between each group’s mean cluster-level percentage knowledge score regarding correct and appropriate knowledge about usage of antibiotics for animal health and antibiotic-related environmental considerations.

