##### Outcome treatment effects

When estimating treatment effects on our trial outcomes we will include all clusters and participants and analyze them according to their original cluster-randomized allocation, unless explained otherwise. This is to ensure that treatment effect estimates are pragmatic and reflect the likely effect of the intervention under real-world conditions, when communities and individuals may not participate in the intervention. It also preserves the benefits of the randomized design (45).

We will estimate all treatment effects based on a contrast between a suitable summary measure of the outcome in the intervention group compared to the control group at endline, and we will use baseline outcome and covariate data to create covariate-adjusted treatment effect estimates. We treat these covariate-adjusted results as our primary evidence about the causal effects of the intervention, as they typically provide increased precision and reduce the biasing impact of any imbalances between treatment groups in terms of the distributions of potential outcomes and participant/cluster characteristics that are causally related to the endline outcomes (46). We will also produce corresponding covariate-unadjusted estimates, where appropriate, and treat those as sensitivity analyses. As recommended by the *Consort 2010 statement: extension to cluster randomized trials* (47), for all binary outcomes we will compute treatment effects on both the difference and ratio scales (both adjusted and unadjusted for covariates).

When making judgments about the likely treatment effects in the target populations of interest we will focus on treatment effect point estimates and their 95% confidence intervals (48). However, for interested readers we will also compute and present the corresponding two-sided *p*-values for those treatment effects (computed based on the null hypothesis of no difference between treatment groups). We will also present a summary measure of each outcome within each treatment group at baseline and endline based on the summary measures contrasted for the treatment effect.

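### For the child antibiotic-use outcome, and possibly the adult and feed outcomes, the baseline covariate rests on very few respondents and may be undefined in some clusters

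*Protocol article*

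**What the plan says.** Under *Subgroup-specific secondary outcomes*, one two-stage recipe covers all outcomes that are valid only in part of the sample. The first stage models subgroup membership among all participants. Its covariate list ends with "number of individuals living in the household, and the cluster-level baseline mean of the relevant secondary outcome". The second stage, fitted to subgroup members only, includes "covariates for the selection bias adjustment factor and all the covariates included in the first stage model". The baseline mean therefore enters twice.

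The outcome definitions set who can contribute to that mean. The adult antibiotic-use outcome needs awareness of antibiotics and "having suffered from either a “sore throat,” “chest cold” or a “common cold” in the past 3 months, and sought treatment for that illness". For the child outcome, "This outcome only applies to the subgroup of female individuals, who report being aware of what an antibiotic is", and she must also have a child under 15 with such an illness that was treated. The feed outcome needs awareness of both antibiotics and antibiotic resistance (ABR). Antibiotic sharing needs awareness of antibiotics only, and water sharing needs household animals.

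Each survey aims for "44 participants per cluster (22 per village), so 1,100 participants across 25 clusters per treatment group and 2,200 participants across all 50 trial clusters", and *Sample size* adds that "we plan to sample an equal number of female and male participants per village". Endline participants must not have taken part at baseline.

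**The concern.** A baseline mean of a subgroup outcome exists only where the cluster's baseline sample contains someone in that subgroup. Each added condition shrinks that group. With nobody eligible, the covariate is zero divided by zero. With a handful, it exists but is imprecise. The two surveys sample different people, so no individual baseline value can take its place.

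An undefined value has consequences beyond the subgroup. The covariate is already in the first-stage model, so a complete-case fit would lose every endline participant in that cluster (about 44), not just the eligible ones. The child and adult outcomes are also the trial's reported antibiotic-use measures for respiratory illness, and the Discussion calls reliance on knowledge outcomes possibly the most important design limitation.

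**Working it through.** **Stated figures.** 44 × 25 = 1,100 per group and 44 × 50 = 2,200 in total, as the protocol says. No subgroup size per cluster is stated.

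**Inputs from the document.** 44 respondents per cluster; equal sexes, so about 22 women; about half of adults aware of antibiotics (2018 survey, *Antibiotic awareness*). Hence 44 × 0.5 = 22 aware adults and 22 × 0.5 = 11 aware women per cluster.

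**Assumptions, not in the document.** Rates are taken as independent of awareness, at low, middle and high levels:
- recent respiratory illness: 0.2, 0.4, 0.6
- treated, given illness: 0.5, 0.7, 0.9
- woman has a child under 15: 0.5, 0.6, 0.75
- ABR awareness among the aware: 0.10, 0.25, 0.50, 0.75
- household owns animals: 0.3 to 0.9

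**Formulas.** The expected number eligible per cluster is n × p. The chance that a cluster is empty is (1 − p)^n, and multiplying by 50 gives the expected number of empty clusters. The chance of 1 to 4 eligible is the matching binomial sum.

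**Child outcome (n = 22 women).**
- Low: p = 0.5 × 0.5 × 0.2 × 0.5 = 0.025; 0.975^22 = 0.573; × 50 = 28.6 empty.
- Middle: p = 0.5 × 0.6 × 0.4 × 0.7 = 0.084; 0.916^22 = 0.145; × 50 = 7.3 empty.
- High: p = 0.5 × 0.75 × 0.6 × 0.9 = 0.2025; 0.7975^22 = 0.0069; × 50 = 0.3 empty.

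**All outcomes.** The last column lets cluster awareness follow a beta distribution with mean 0.5 and ICC 0.3 (simulated). The protocol gives 0.3 for the two primary knowledge scores only; using it for awareness is an upper sensitivity value.

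| Outcome | Mean eligible per cluster | Empty / 1–4, equal awareness | Empty / 1–4, awareness ICC 0.3 |
|---|---|---|---|
| Child, low | 0.6 | 28.6 / 21.3 | 30.0 / 20.0 |
| Child, middle | 1.8 | 7.3 / 41.1 | 12.1 / 34.2 |
| Child, high | 4.5 | 0.3 / 26.2 | 4.6 / 22.2 |
| Adult, low | 2.2 | 5.2 / 41.4 | 10.3 / 33.5 |
| Adult, middle | 6.2 | 0.07 / 12.1 | 3.2 / 16.2 |
| Adult, high | 11.9 | 0 / 0.2 | 1.5 / 7.7 |
| Feed, ABR 0.10 | 2.2 | 5.2 / 41.4 | 10.3 / 33.5 |
| Feed, ABR 0.25 | 5.5 | 0.1 / 17.0 | 3.7 / 18.2 |
| Feed, ABR 0.50 | 11.0 | 0 / 0.4 | 1.7 / 8.4 |
| Feed, ABR 0.75 | 16.5 | 0 / 0 | 1.0 / 5.3 |
| Antibiotic sharing | 22 | 0 / 0 | 0.7 / 3.8 |
| Water sharing | 13–40 | 0 / 0 | not run |

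The child outcome is recorded per child, so a cluster may have more records than women. The chance of an empty cluster is unchanged.

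**Precision of a small mean.** Reliability = n × ICC / (1 + (n − 1) × ICC), with the outcome ICC assumed.
- ICC 0.05: 0.10/1.05 = 0.10 for two people, 0.20/1.15 = 0.17 for four, 2.2/3.15 = 0.70 for 44.
- ICC 0.3: 0.6/1.3 = 0.46, 1.2/1.9 = 0.63 and 13.2/13.9 = 0.95.

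**The case against.** The analysis section describes itself as a summary ahead of a statistical analysis plan, and a rule for an undefined covariate could properly sit there. That stands as far as the missing rule goes. It does not remove the point, because the covariate is specified here, and a missing-value rule would leave the child outcome adjusted on one to four women in many clusters.

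A reader might go further in four ways that the documents do not support.

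- *That the plan contradicts its own principle that* "we will include all clusters and participants and analyze them according to their original cluster-randomized allocation". That sentence goes on to allow exceptions explained elsewhere, and no text says clusters will be dropped. Loss of clusters is an inference from complete-case fitting.
- *That the treatment comparison is biased by arm.* The baseline survey precedes randomization, so which clusters are empty cannot depend on allocation. The bootstrap can still resample clusters 1:1 within subdistricts; fewer of them would enter the fit.
- *That all subgroup outcomes are affected.* Antibiotic sharing and water sharing have ample baseline respondents.
- *That a small-cluster mean is mostly noise.* That is true at an outcome ICC of 0.05 but not for four people at 0.3, where reliability is 0.63. The documents give no ICC for these outcomes.

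**Conclusion.** The point holds for the child antibiotic-use outcome. Over the whole assumed range the mean number of eligible baseline women is below five per cluster. About 0.3 to 29 of 50 clusters have no value, and about 21 to 41 rest on one to four women. Even at the most favourable rates, about half the clusters have such a small base.

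For adult antibiotic use and feed it is conditional. It matters if illness and treatment rates are low, if about a quarter or fewer of aware adults know of ABR, or if awareness varies strongly between clusters. One cannot say from the documents that the baseline survey is unable to supply the value for these outcomes.

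The cost is weaker adjustment and, under complete-case fitting, lost clusters that tend to be those with low baseline awareness or little reported illness. That affects precision and representativeness. The primary outcomes are untouched and the secondary outcomes are declared exploratory, so severity is minor.

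**What to change.** Baseline data are already collected, so count the eligible baseline respondents per cluster for the child, adult and feed outcomes. This needs no endline data.

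For the child outcome, and for the adult and feed outcomes if the counts show empty or very small clusters, replace the own-outcome baseline mean in both stages with a cluster-level baseline value that all respondents supply. The proportion aware of antibiotics or the mean of primary outcome 1 would serve. State that no cluster is to be lost through an undefined baseline covariate. Keep the own-outcome mean for antibiotic sharing and water sharing.

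The cost is a sentence or two in the analysis plan and no new data. The drawback is that the replacement is a different quantity from the outcome and may be less directly prognostic, though it is measured on about 44 people in every cluster.

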We will then fit a second-stage generalized linear model with Poisson errors and a log link to the primary outcome of interest. However, instead of the percentage knowledge scores as outcome values we will analyze the raw count of correct/appropriate answers, as appropriate for the Poisson distribution. The model will contain covariates for whether the participant reported attending one or more CDs (yes/no), the residual computed in the first-stage model, and all the other covariates included in the first-stage model.

Using this model, we will then use marginal effects methods to estimate the treatment effect by computing each participants’ model-predicted count of correct/appropriate answers based on their observed covariate values except for attending one/more CDs, which will be first set to yes for all participants (and predictions saved) and then no for all participants (and predictions saved). We will then convert these predicted counts of correct/appropriate answers to predicted percentages of correct/appropriate answers by dividing by the relevant number of questions asked for that knowledge score and multiplying by 100. Lastly, we will take the mean of each set of predictions and take their difference. This will estimate the causal effect of attending one/more CDs as the mean difference in the relevant percentage knowledge score for those attending one/more CDs compared to those attending no CDs, among those who would be predicted to always attend CDs if they were available in their community.

As a sensitivity analysis we will also repeat these analyses but at the second stage use generalized linear models with Gaussian errors and identity links instead, with the relevant percentage knowledge scores as the outcome, to compare with the results based on the Poisson model.

For statistical inference we will estimate 95% confidence intervals for all these treatment effects via a stratified, clustered bootstrap approach (52), to account for the clustered structure of data. This will involve resampling clusters within subdistricts while maintaining a 1:1 treatment allocation of the clusters within each bootstrapped subdistrict dataset, and using a modification of the bias-corrected accelerated method to compute the 95% confidence intervals from the bootstrapped data (53) (based on 5,000 resamples).

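### Subgroup-specific secondary outcomes: cluster weights enter the regression but not the averaging of predictions, so the result need not be the declared cluster-average effect

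*Protocol article*

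**What the plan says.** All of this is in the protocol article, under Statistical analyses.

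- **Target.** Subgroup-specific secondary outcomes: "Our approach aims to estimate the cluster-average causal effect of treatment among the subgroup of individuals" who would belong to it whatever the intervention did. The measure is described "as the difference/ratio in the cluster-level percentage occurrence of the relevant outcome event between treatment groups".
- **Analysis set.** Same section: "We will then subset the data to only include those participants who are in the subgroup for which the ultimate outcome is valid".
- **Outcome model.** A logistic model. "This model will include covariates for the selection bias adjustment factor and all the covariates included in the first stage model". Those covariates include individual characteristics, subdistrict and a cluster-level baseline mean.
- **Weights.** Same section: "this model will also be weighted by the inverse of the cluster sample sizes to produce cluster-average causal effect estimates".
- **Averaging.** The section then refers back, for the marginal-effects step, to Effect of engagement with the community dialogue approach intervention. That section sets out to estimate an individual-level effect, predicts for every participant, and ends: "Lastly, we will take the mean of each set of predictions and take their difference". It mentions no weights.
- **Cluster size.** The Sample size section fixes the survey sample at 44 per cluster. The number left after subsetting is not fixed.

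**The concern.** The plan says that weighting the regression is what yields a cluster-average effect. In a logistic model with covariates, the risk difference and risk ratio depend on two things: the fitted coefficients, and the covariate distribution over which predictions are averaged. The stated weights act on the first only. A plain mean over records gives a cluster with 30 subgroup members three times the influence of a cluster with 10.

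The plan handles the whole-sample binary outcomes differently: predicted probabilities are first averaged within each cluster. No such step appears for the subgroup outcomes.

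At stake is whether the number labelled cluster-average is one. The general principles also commit the trial to reporting each arm's summary measure, so the arm-level risks would be published too.

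A second, smaller point is that cluster sample size is not defined. If it meant the 44 people surveyed, the weights would be constant and do nothing.

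**Working it through.** The protocol gives no figure for these outcomes, so there is none to reproduce. Numbers below marked as assumed are not in the protocol.

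**1. The two averages.** Let p_ij be the predicted probability for record i in cluster j, n_j the records analysed in that cluster, and J the number of clusters.

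- Plain mean: Σ_j Σ_i p_ij / Σ_j n_j = Σ_j (n_j / Σn) × p̄_j. Clusters count in proportion to n_j.
- Mean weighted by 1/n_j: (1/J) Σ_j p̄_j. Clusters count equally.

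They agree if treatment is the only covariate, because every record in an arm then has the same prediction. With the plan's covariates they generally differ.

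**2. Exact example (assumed).** Two cluster types in equal number, with 10 and 30 subgroup members, control risks 0.60 and 0.30, and log odds ratio −0.6 in both.

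- exp(−0.6) = 0.5488.
- Intervention risk, first type: odds 1.5 × 0.5488 = 0.8232, risk 0.4515.
- Intervention risk, second type: odds 0.4286 × 0.5488 = 0.2352, risk 0.1904.
- Equal cluster weight: (0.4515 + 0.1904)/2 = 0.321 against (0.60 + 0.30)/2 = 0.450. Difference −0.129, ratio 0.713.
- Plain mean (weights 0.25 and 0.75): 0.256 against 0.375. Difference −0.119, ratio 0.682.

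**3. Simulation, risk lower where the subgroup is larger (assumed).** 50 clusters of 44 and 400 replicates per scenario, with log odds ratio −0.6, constant or varying with subgroup size. The regression is weighted by 1/n_j throughout; only the averaging differs. Risks are intervention / control in %. Share is the approximate fraction of respondents in the subgroup. SD is the between-cluster SD of membership on the logit scale.

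| Share | SD | Odds ratio | Weighted averaging: risks; RD; RR | As written: risks; RD; RR |
|---|---|---|---|---|
| half | 0.8 | constant | 32.1 / 45.3; −13.14; 0.710 | 27.9 / 40.5; −12.61; 0.689 |
| half | 0.8 | varying | 34.2 / 45.3; −11.12; 0.755 | 28.9 / 39.6; −10.63; 0.731 |
| quarter | 0.8 | constant | 32.8 / 45.4; −12.62; 0.722 | 26.5 / 38.3; −11.74; 0.693 |
| half | 1.2 | constant | 32.5 / 45.1; −12.56; 0.721 | 26.9 / 38.8; −11.89; 0.693 |
| half | 1.2 | varying | 34.5 / 45.6; −11.14; 0.756 | 27.3 / 37.8; −10.49; 0.723 |
| quarter | 1.2 | constant | 32.3 / 45.2; −12.97; 0.713 | 24.2 / 35.9; −11.72; 0.674 |

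Arm risks shift by 4.2 to 9.3 points, the difference by 0.49 to 1.25 points and the ratio by 0.02 to 0.04. In the fourth row the true cluster-average risks are 32.5 / 45.3, which weighted averaging recovers.

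In the fifth row the true ratio is 0.757 cluster-average and 0.654 participant-average. The written method gives 0.723, matching neither.

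In a further run where the cluster baseline covariate did not predict risk, the two versions nearly agreed (RD −10.19 and −10.07). The shift works through the covariates.

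**4. Simulation, risk higher where the subgroup is larger (assumed).** 300 replicates, mean awareness 50%, log-odds effect −0.6. Gradient is the rise in outcome log-odds per SD of cluster awareness.

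- Awareness ICC 0.3, gradient 0.5: control risk 51.9% as written against a true 45.4%; difference −14.2 against −13.4; ratio 0.73 against 0.71. Weighted averaging gave 45.5% and −13.4.
- Gradient 0.8: control risk 55.1% against 45.6%; difference −13.8 against −12.5.
- ICC 0.1, gradient 0.5: control risk 49.1% against 45.3%.

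The shift in arm risks reverses with the assumed association, so its direction cannot be stated in advance.

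Neither simulation ran the plan's full model. The selection adjustment factor and strata were left out of the one in step 3, and the model in step 4 had only treatment and cluster awareness.

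**The case against.** The strongest reply is that the article only summarises, promises a statistical analysis plan and defers to a cited method paper. Whether weights go into the averaging call could be left to that plan. The cross-reference also cannot be literal: the engagement section predicts Poisson counts and switches dialogue attendance, and it forms only a difference. The cluster-level percentage measure stated for the subgroup outcomes could then be read as implying cluster-level averaging.

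This shows that the right estimator is compatible with the stated aim. It does not remove the mismatch. The article names the target, says where the weights go, says that this placement achieves the target, and points to an averaging rule built for a different target.

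Two stronger readings are tempting and are not supported.

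- **That differences and ratios simply weight clusters by subgroup size.** If the weights use analysed subgroup size, the treatment coefficient is still estimated with clusters weighted equally. The result is a hybrid.
- **That the weights are constant at 1/44 and the effect is far off.** The weighting sentence follows the subsetting step and states a purpose that constant weights would defeat, so analysed size is the natural reading. The large discrepancies (−19.6 against −14.4 points, or −17.2 against −14.2) need the strained reading plus an assumed effect gradient of −0.4 log-odds per SD of awareness.

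It also stands that the shift in the contrast is modest beside sampling error. With an assumed 550 aware respondents per arm (half of 1,100) and risks of 0.45 and 0.32, the standard error of the difference before clustering is √(0.45×0.55/550 + 0.32×0.68/550) = 0.029, about 3 points.

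**Conclusion.** The point holds as a mismatch between declared estimand and described procedure, confined to the subgroup-specific secondary outcomes. When subgroup size is associated with outcome risk or treatment effect, and the covariates carry that association, the written steps need not return the cluster-average effect. With no association there is no bias.

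Under the assumed scenarios the arm-level risks move by about 4 to 10 points in an unknown direction, the difference by about 0.5 to 1.3 points and the ratio by about 0.02 to 0.04. The protocol reports only that about half of adults were aware of antibiotics. It does not say how awareness varies between clusters or how it relates to these outcomes, and its ICC of 0.3 was assumed for the knowledge scores. The sizes are therefore illustrations.

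The primary and whole-sample secondary analyses are untouched, and the plan treats all secondary outcomes as exploratory. The correction is still worth making because it costs almost nothing and makes the label true.

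**What to change.** In the analysis plan:

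1. Define the weight as 1/(number of records analysed in the cluster after subsetting), counting children for the child outcome.
2. After predicting under intervention and under control, average the probabilities within each cluster and then equally across clusters, before forming the difference and ratio. Applying the same weights in the averaging is equivalent.
3. Repeat both steps in every bootstrap resample, recomputing the cluster counts.

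This takes a sentence or two of text and one argument in the averaging code, with no new data. The downside is slightly wider intervals where some clusters have few subgroup members.
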